##### Identification of AE's related to care provided outside the ED

If the outcome determination as outlined above indicates the patient suffered an AE related to non-ED care, physicians from the appropriate service involved will also review these cases. For example, for all patients whose AE was deemed to be related to care provided during their inpatient stay, these cases will be further reviewed by a hospitalist paediatrician. These cases will be further discussed if consensus between the ED physician and service specific physician on outcome is not obtained.

##### Identification of AE's in patients with mental health entrance complaints

These cases will be reviewed by 2 ED physicians and a psychiatrist (rather than only ED physicians). The same methodology as outlined above will be used to determine if the patient suffered an AE.

### Data quality and training of research staff

Computerised, web-based data collection forms (through REDCap) will be used throughout this study to ensure complete data entry. Portable tablets (iPads) will be used to collect all data and embedded logic safeguards will ensure variables are entered within predetermined limits. Warning messages will prompt the user for any incomplete fields. Standardisation of study methods will be achieved through training in all activities and outcome tools used by research staff. Research nurses applying the CPPT for admitted patients will be trained using a standard set of medical records and a training manual. Interobserver reliability of use of the CPTT will be assessed during the training session and on a random selection of 10% of records throughout the study. Case summaries prepared by the site research nurse will be reviewed until 10 consecutive summaries accurately reflect the medical record and then 5% will be randomly reviewed for integrity. If case summaries are found to have discordant information, remedial instruction will be given and all case summaries will be reviewed until 10 consecutive records are accurate, at which time the random screening will recommence. Physician outcome reviewers will receive training in definitions, use of cases for practices and discussion of discrepancies in outcome coding. Interobserver reliability of physician determination of AE will be assessed during the training session and on a random selection of 5% of records throughout the study.

### Sample size

The primary outcome is a proportion, the occurrence of AEs related to ED care among a cohort of ED patients. In our recent systematic review, we found that 0.16–6.0% of ED patients had an AE related to ED care.^24^ Studies using medical record review determination of AEs, versus surveillance or active reporting, consistently find the highest proportion of patients with AEs. Among the highest quality ED-based studies, the AE rate ranged from 5% to 6.0% (primarily adult patients). The only Canadian study of AE among admitted children found that overall 9.2% of children had an AE. While it would be ideal to consider clustering by shift in our sample size calculation, it is not possible due to lack of data. Because of this and also given the range of AEs reported among ED patients, we have chosen to be conservative in our sample size estimates. We will aim to enrol 5632 patients over a 1-year period and assume a 10% loss to follow-up. This will allow us detect a proportion of patients with an AE related to care provided in the ED of 5% to within an absolute margin of error of 0.6% (with 95% CI).

### Data analysis

#### Outcome analysis

Descriptive statistics will be used to describe enrolled patients. The primary outcome, the proportion of children with AEs related to ED care, will be reported with 95% CIs, accounting for the stratified cluster sampling design using SAS PROC SURVEYFREQ. Estimates of design effect will be examined. Secondary outcomes will be similarly estimated. To explore the association with AE and preventable AE of patient-level and system-level characteristics (together and separately) we will use univariate methods (PROC SURVEYFREQ) and multiple logistic regression (PROC SURVEYLOGISTIC). With sample size at follow-up of 5069, and an anticipated 5% rate of AEs, we expect approximately 253 AEs. Following the recommendation that approximately 10 events are required for each variable included in a multivariate model^38^ will allow us to include up to 25 predictor variables. Similar analyses will also be performed for preventable AEs. If 50% of AEs are preventable, we would expect approximately 126 preventable AEs, allowing us to include 12–13 predictor variables. Factors significant at the two-sided p<0.10 level on univariate analysis will be considered for inclusion in the multivariate model. When variables are highly correlated, the less clinically relevant ones will be omitted. Patient characteristics (see online supplementary appendix 2) to be examined include age, sex, language, immigration, triage level, time, weekday/weekend presentation, discharge disposition, pre-existing mental health condition, pre-existing health condition, use of any prescription medications and complex illness.^7^ System-level factors (see online supplementary appendix 2) measurable for each individual patient include length of time to see physician, number of ED staff physicians involved in that patient's care, number of ED physicians (trainees and staff) involved in that patient's care, location within the ED, need for a consultation, number of services consulted, level of physician initially managing the patient and delay to ambulance off-load for patients arriving by ambulance. System level factors pertaining to the environment of the ED around the time of patient arrival that may be markers of crowding include the overall ED census, number of patients waiting to be seen, number of patients awaiting in-patient beds and average time between patient triage and registration. Since these environmental factors may depend on the size of the ED, we will also consider as a variable the number of beds in the ED.

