##### Heath care system data

Given concerns that ED crowding has adverse outcomes for patients,^15–22^ we will attempt to measure crowding in several ways. For feasibility reasons, we will collect some data items at the midpoint of the hour of triage: specifically the number of patients in the ED, number waiting to be seen by a physician, number awaiting in-patient beds and average length of time between triage and registration. We will also collect data on the length of time for initial physician assessment of the patient, the area of the ED to which patient is triaged (participating EDs are divided into high and low acuity zones, most with separate space and staffing), ambulance off-load type (for patients who arrive by ambulance), type of first healthcare provider assessing the patient (eg, trainee, physician and nurse practitioner), training level of first physician assessing the patient (trainee vs staff), number of ED and consulting physicians involved in patient care, number of end of physician shift handovers for each patient, time between consult request and consultant arrival time to disposition decision, length of ED stay and discharge disposition. We will also collect information regarding the staffing of the ED during each shift (ie, number of nurses present during a study shift, number of staff physicians and number and level of medical trainees).

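### The only procedure named for the p<0.10 univariate screen is a frequency-table procedure, so numeric predictors, including all four crowding markers, must be grouped or tabulated by value, usually at a cost in power

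*Protocol article*

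**What the plan says.** The protocol article, Outcome analysis, describes the exploration of characteristics associated with adverse events (AEs) and preventable AEs in these terms: "we will use univariate methods (PROC SURVEYFREQ) and multiple logistic regression (PROC SURVEYLOGISTIC". PROC SURVEYFREQ is the only procedure attached to the univariate step, and PROC SURVEYLOGISTIC is attached to the multiple regression. The screening rule is: "Factors significant at the two-sided p<0.10 level on univariate analysis will be considered for inclusion in the multivariate model".

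The same section lists the candidates.

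- Three of the four crowding markers are counts: "overall ED census, number of patients waiting to be seen, number of patients awaiting in-patient beds". The fourth is a mean time, from triage to registration.
- ED size enters as well: "we will also consider as a variable the number of beds in the ED".
- The system factors measured for each patient "include length of time to see physician, number of ED staff physicians involved in that patient's care", then further counts and categories, and "delay to ambulance off-load for patients arriving by ambulance".
- Age is among the patient characteristics.

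The section on health care system data describes the crowding items as collected in raw form: "specifically the number of patients in the ED, number waiting to be seen by a physician, number awaiting in-patient beds", plus the average triage-to-registration time. Definitions of the characteristics are referred to online supplementary appendix 2. The text shown gives no cut points and no other univariate procedure.

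**The concern.** PROC SURVEYFREQ builds tables and tests them with design-adjusted chi-square tests. It has no linear term for a numeric predictor. A count such as the ED census, or a time such as the wait for a physician, can go through it in only two ways. It can be grouped, which discards the ordering and spacing within groups, or it can be tabulated at each observed value, which gives a sparse table with many degrees of freedom.

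The test at this step is also the screen for the multivariable model, so lost power here becomes a lower chance that a real association reaches that model. The variables that suit the procedure least are those that carry the crowding question. The article names crowding as a concern, and associated characteristics are a listed secondary outcome. This is more than detail left to another document: the text names a procedure that does not suit several of the variables assigned to it, while a suitable one is already in the plan.

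**Working it through.** **The plan's own figures.**

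- Sample size section: n = 1.96² × 0.05 × 0.95 / 0.006² = 5068.8, so 5069. With 10% loss, 5632 × 0.9 = 5068.8, again 5069.
- Outcome analysis section: 0.05 × 5069 = 253.5 (stated 253), which at 10 events per variable gives 25 predictors. Half of 253 is 126.5 (stated 126), which gives 12–13 predictors.

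These all reproduce. The article states no power for the screening step.

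**Assumptions, because the document gives no values.** The predictor is normal and its effect log-linear. The odds ratio (OR) is 1.10 to 1.25 per SD. The design effect is 1, with 1.5 as a check.

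**Formula.** For a linear logistic term (1 df) the noncentrality is λ = N p(1−p) (ln OR)² / design effect, with N = 5069 and p = events/5069. N p(1−p) is 240.4 for 253 events and 122.9 for 126 events. For k equal groups tested as nominal, the noncentrality is λ × R_k on k−1 df. The information retained, R_k, is 0.637 (2/π), 0.793 and 0.861 for k = 2, 3 and 4. Power is the chance that the noncentral chi-square exceeds its 10% critical value: 2.71, 4.61 and 6.25 for 1, 2 and 3 df.

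**Example.** With OR 1.15 and 253 events, λ = 240.4 × (ln 1.15)² = 4.70, so power is 70% for the linear term. A median split gives 4.70 × 0.637 = 2.99 on 1 df, so 53%. Quartiles give 4.70 × 0.861 = 4.04 on 3 df, so 49%.

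**Power to pass p<0.10, design effect 1**

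| Events | OR per SD | Linear, 1 df | Median split | Tertiles | Quartiles |
|---|---|---|---|---|---|
| 253 | 1.10 | 44% | 32% | 30% | 28% |
| 253 | 1.15 | 70% | 53% | 52% | 49% |
| 253 | 1.20 | 88% | 73% | 72% | 70% |
| 253 | 1.25 | 97% | 87% | 87% | 86% |
| 126 | 1.10 | 28% | 22% | 20% | 19% |
| 126 | 1.15 | 46% | 34% | 32% | 30% |
| 126 | 1.20 | 65% | 49% | 47% | 44% |
| 126 | 1.25 | 80% | 63% | 62% | 59% |

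With design effect 1.5 and OR 1.20, power is 75% (linear), 58% (median split) and 53% (quartiles) for 253 events, and 50%, 37% and 33% for 126 events.

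**Simulation check** (1000 replicates, unclustered, OR 1.20). For a normal predictor, power was 88% continuous against 70%, 72% and 67% for 2, 3 and 4 groups with a 5% event rate, and 65% against 50%, 48% and 44% with a 2.5% rate. Type I error stayed near 10% throughout. For an assumed lognormal predictor whose effect is linear on the raw scale, power was 95% against 64–67%, and 79% against 40–43%. If the effect is linear on the log scale instead, the normal-predictor figures apply.

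**Splines.** An overall test of a 3-knot spline has 2 df and of a 4-knot spline 3 df. When the true effect is linear they gain no noncentrality. At OR 1.15, power is 60% and 54% with 253 events, and 38% and 34% with 126 events. The 4-knot spline is therefore close to the median split (53% and 34%).

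**The case against.** The strongest reply is that a software name in brackets is thin evidence, that the article is condensed, and that appendix 2 may define clinical categories. In part this stands. Cut points cannot be called arbitrary without seeing the appendix. But categories set there would confirm the grouping rather than remove its cost.

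Several stronger readings are tempting, and the document does not support them.

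- *Every time and count factor is affected alike.* Off-load is recorded at the index visit as a type, so its delay may be categorical. Numbers of physicians or services may be small counts that can be tabulated without cut points, with a smaller loss. In an assumed three-level example, power falls from 75% to 66%. Bed count is a site-level variable over nine sites.
- *The screen decides entry to the model.* Factors that pass are only considered for inclusion, and clinical relevance decides between highly correlated ones.
- *Finer categories would make the loss small.* They retain more information, but the added degrees of freedom use it up. Tertiles and quartiles do no better than a median split, apart from a negligible difference at OR 1.25.
- *Any continuous form recovers the loss.* The gain belongs to the 1-df linear term; a 4-knot spline under a linear effect recovers almost none of it.
- *Grouping always costs power.* With a threshold or U-shaped effect it may lose nothing, or gain.
- *The main result is at risk.* The primary proportion, its confidence interval and the sample size do not use this step.

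**Conclusion.** The point holds as a minor one. As written, the univariate step names a table procedure for predictors that include four crowding markers, time to physician and age, all numeric as named. With no design effect and OR 1.10 to 1.25 per SD, a median split lowers the chance of passing the screen by about 10 to 17 percentage points with 253 events and 6 to 17 with 126. Nominal quartiles lower it by about 11 to 21 and 9 to 21. These sizes rest on assumed effect sizes, a normal predictor and a log-linear effect, none of which the document gives. They would be larger for a skewed predictor with a raw-scale linear effect, and absent or reversed for a threshold effect. The reach is confined to the exploratory association analysis.

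**What to change.** State in the Outcome analysis section that numeric factors are screened with one-variable PROC SURVEYLOGISTIC, using the same strata and clusters as the other analyses. Keep them continuous with a prespecified linear (1-df) term, transformed where the distribution is skewed. Reserve PROC SURVEYFREQ for categorical factors, and say in appendix 2 which factors are which.

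Use a spline only where non-linearity is expected in advance, and count its extra parameters against the budgets of 25 predictors for AEs and 12–13 for preventable AEs.

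For linear terms the cost is wording, since the procedure is already in the plan. A spline carries a real cost: 2 or 3 parameters in place of 1, which matters most for preventable AEs. No change to data collection, sample size or the primary analysis is needed.

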## Introduction

Patient safety has been identified internationally as a healthcare priority.^1^
^2^ Adverse events (AEs), broadly defined as unintended harm to the patient that is related to healthcare and/or services provided to the patient rather than the patient's underlying medical condition,^3^ represent a significant threat to patient safety and public health.^4–7^ Canadian data suggest 7.5% of hospitalised adults suffer AEs and one-third of these events are preventable.^6^ On a national level, this represents up to 23 750 preventable deaths per year among hospitalised adults.^6^ Recent data demonstrate that Canadian children are also at high risk with 9.2% of children admitted to hospital suffering an AE and almost half of these events are preventable.^7^ The economic burden of AEs is also high. From 2009 to 2010, the cost of AEs in the Canadian acute care system was estimated at $1.1 billion.^8^

To date, patient safety research has focused primarily on admitted patients. However, most Canadians, and especially children, are more likely to visit an emergency department (ED) than to be admitted to hospital. Of the over 16 million annual patient visits to EDs in Canada, only 9.2% result in admission.^9^ The ED is considered a high-risk setting for AEs due to variable provider experience, visits ‘outside of regular hours’, high patient volume, and a chaotic work environment characterised by frequent interruptions.^10–14^ The need for ED-based patient safety research is made more pressing by increasing demands on the ED system. ED crowding and long wait times have been linked to increased patient mortality,^15–19^ treatment delays^20–22^ and ambulance diversions.^23^

Only one systematic review of the prevalence, preventability, severity and types of AEs in the ED has been published.^24^ The proportion of ED patients who suffered at least one AE related to care provided in the ED varied widely between the studies included in this review, ranging from 0.16% to 6.9% of all patients. No study in the review examined how commonly AEs occurred among children presenting to the ED. The results of this review also suggest that a large proportion (36–71%) of AEs may be preventable and this is at least comparable to that reported in hospitalised patients (35–51%).^4–6^
^25^ The review also suggested that the types of AEs that occur in the ED may be different than in hospitalised patients, and different between discharged and admitted ED patients.

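### No stated multivariable model adjusts crowding for patient confounders without also admitting time to physician and other post-arrival variables, so the meaning of the crowding odds ratio is left to the selection rules

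*Protocol article*

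**What the plan says.** The protocol article treats crowding as something to be studied. The Introduction states that "ED crowding and long wait times have been linked to increased patient mortality", and continues the list with treatment delays and ambulance diversions. The section on health care system data begins "Given concerns that ED crowding has adverse outcomes for patients" and describes several measures. Secondary outcome measures ends with the patient and system characteristics associated with AEs and with preventable AEs.

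Outcome analysis sets out the models: "patient-level and system-level characteristics (together and separately) we will use univariate methods (PROC SURVEYFREQ) and multiple logistic regression (PROC SURVEYLOGISTIC". It names three groups of candidates:

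- **Patient characteristics (12):** "age, sex, language, immigration, triage level, time, weekday/weekend presentation, discharge disposition, pre-existing mental health condition", followed by pre-existing health condition, prescription medication use and complex illness.
- **System factors measured per child (8):** "System-level factors (see online supplementary appendix 2) measurable for each individual patient include length of time to see physician", followed by two counts of physicians, location in the ED, need for consultation, number of services consulted, level of first physician and ambulance off-load delay.
- **System factors describing the ED around the child's arrival (4, plus number of beds):** the "markers of crowding include the overall ED census, number of patients waiting to be seen, number of patients awaiting in-patient beds" and the average time from triage to registration. Number of beds is added because these counts may depend on ED size.

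Two rules govern entry: "Factors significant at the two-sided p<0.10 level on univariate analysis will be considered for inclusion in the multivariate model" and "When variables are highly correlated, the less clinically relevant ones will be omitted". Neither separates conditions at arrival from what happens to the child afterwards.

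**The concern.** The crowding markers describe the ED when the child arrives. Time to physician, location, level and number of physicians, consultation and disposition are determined later, and crowding may affect several of them. If part of any harm from crowding runs through a longer wait, a model holding both gives only the part of the crowding association that does not run through waiting. A model without the wait gives the total. These are different quantities, and a reader asking whether crowded EDs are less safe usually wants the total.

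The plan does not say which it will report. The selection rules decide, so the answer could change with the data and could differ between the all-AE and preventable-AE models. A statement that crowding is not independently associated with AEs could then reflect adjustment for waiting.

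**Working it through.** **1. The plan's own figures.** Precision: 1.96² × 0.05 × 0.95 / 0.006² gives 5069, and 5069 / 0.9 = 5632.2, against the stated 5632. Expected AEs: 5069 × 0.05 = 253.45, or 25 predictors at 10 events each. Preventable AEs: 253.45 × 0.5 = 126.7, or 12.7 predictors. All reproduce.

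**2. Does the predictor limit keep crowding and waiting apart?** Named candidates: 12 + 8 + 4 + 1 = 25, equal to the all-AE limit. The system-level set alone is 8 + 4 + 1 = 13, about the preventable-AE limit of 12–13. Counted by name, the limit does not separate them in the all-AE model or in a system-only model for preventable AEs. In the combined preventable-AE model not all can enter, and no order of priority is given.

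**3. The stated analyses, side by side.**

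| Analysis | Crowding | Patient confounders | Time to physician and other process variables |
|---|---|---|---|
| Univariate | yes | no | no |
| Patient-level only | no | yes | only discharge disposition |
| System-level only | candidate | no | candidates |
| Combined | candidate | candidates | candidates |

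No row gives crowding with patient confounders and without process variables. For time of day and weekday/weekend, the patient-level row gives adjustment for age, sex, triage level and conditions without time to physician. Its one post-arrival candidate is discharge disposition.

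**4. Size, on assumed inputs.** With a direct log odds ratio d for crowding, a path a from crowding to wait and a log odds ratio b for wait on AEs (all per SD), the total is approximately exp(d + a × b), and the wait-adjusted value is about exp(d). Take d = 0.1, so exp(0.1) = 1.11:

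- a = 0.3, b = 0.2: exp(0.1 + 0.06) = 1.17
- a = 0.5, b = 0.4: exp(0.1 + 0.20) = 1.35
- a = 0.7, b = 0.4: exp(0.1 + 0.28) = 1.46

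A simulation of 400,000 children with one acuity confounder, a from 0.3 to 0.7 and b of 0.2 or 0.4, gave confounder-adjusted totals of 1.17 to 1.47, values with wait included of 1.10 to 1.13, and unadjusted values of 1.26 to 1.54. The total thus differs from both the wait-adjusted and the univariate result.

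**5. At about the study's size.** Assumed: 12 children × 422 shifts = 5064, 5% AEs, odds ratio 1.5 per SD of wait, cluster-robust logistic regression. Ranges span two runs (400 and 200 replicates).

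| Crowding–wait correlation | Direct OR | Without wait: OR (power) | With wait: OR (power) |
|---|---|---|---|
| 0.6 | 1.00 | 1.27–1.28 (94.5–97%) | 1.00 (5–6%) |
| 0.4 | 1.00 | 1.17 (69–70%) | 1.00 (3–4%) |
| 0.6 | 1.10 | 1.40 (about 100%) | 1.10 (20–25%) |
| 0.4 | 1.10 | 1.28–1.29 (96–98%) | 1.09–1.10 (26–27%) |

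The 1.00 values follow from assuming no direct effect. These runs use one crowding variable and apply neither the p<0.10 screen nor the correlated-variable rule, so they show direction and possible scale. They do not predict what the planned analysis will find.

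**The case against.** The case for leaving the plan alone has several parts.

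- **The aim is exploratory.** The plan speaks of exploring associations and claims no causal effect. That stands, and it limits the weight of the point. It does not remove it: an adjusted association is still hard to read when its adjustment set is unknown in advance.
- **Waiting as an intermediate step is assumed.** The Introduction names crowding and long waits side by side, not as a chain, and time to initial assessment is collected in the same paragraph as the crowding measures, so it could be read as another crowding indicator. This stands as a caution. However, Outcome analysis lists time to physician apart from the crowding markers, and adjusting one indicator for another would raise the same problem of interpretation.
- **Joint entry is conditional.** A reader might infer that crowding and time to physician will certainly share a model. The text supports only that both are candidates; either may fail the screen or be dropped for correlation.
- **Off-hours presentation.** A reader might infer that it too lacks any adjusted total association. Time and weekday/weekend are listed as patient characteristics, so on the natural reading of fitting the groups separately, a patient-level multivariable model omits time to physician. Only if the separate fitting meant univariate analysis alone would the stronger reading hold.
- **The article is condensed.** An analysis plan or online appendix 2 may say more. But the article already fixes the candidate groups and the entry rules, and these make no distinction by order in time.

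**Conclusion.** The point holds for crowding. As stated, no multivariable model gives crowding adjusted for patient confounders alone, and the selection rules decide whether its odds ratio is a total or a partial association. If waiting carries part of the effect, adjusting for it moves the odds ratio towards 1; the amounts shown rest wholly on assumed effect sizes and correlations.

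For off-hours presentation only a small residue remains: discharge disposition is a post-arrival candidate in the patient-level model.

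The documents do not support saying that the study will miss a crowding effect. Nor do they support saying that its planned recommendations depend on these regressions: Knowledge translation refers to study findings in general, webinar feedback and a steering committee. The primary AE proportion is unaffected. This is an improvement worth making to an exploratory secondary analysis.

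**What to change.** In Outcome analysis, for each outcome (AE and preventable AE):

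1. Pre-specify a crowding model adjusted for factors fixed at arrival (age, sex, triage level, pre-existing and complex conditions, time, weekday/weekend) and for number of ED beds. The beds term is needed because the plan itself notes that the counts may depend on ED size.
2. Leave out of this model time to physician, off-load delay, location in the ED, level and number of physicians, consultation and discharge disposition.
3. Fit the crowding markers one at a time, or name one lead marker, so that they do not adjust for each other.
4. Add the process variables in a second model, labelled as the association of crowding not explained by them.
5. Do not apply the correlated-variable deletion rule between crowding markers and process variables.
6. In the patient-level model for time and weekday/weekend, leave out discharge disposition.

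This uses data already to be collected and needs no more patients. The cost is a few sentences in the plan and one more model per outcome to report.
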